## Abstract

**Background:**

Rehabilitation strategies after abdominal surgery enhance recovery and improve outcome. A cornerstone of rehabilitation is respiratory physiotherapy with inspiratory muscle training to enhance pulmonary function.

Pre-habilitation is the process of enhancing functional capacity before surgery in order to compensate for the stress of surgery and postoperative recovery. There is growing interest in deploying pre-habilitation interventions prior to surgery.

The aim of this study is to assess the impact of preoperative inspiratory muscle training on postoperative overall morbidity. The question is, whether inspiratory muscle training prior to elective abdominal surgery reduces the number of postoperative complications and their severity grade.

**Methods:**

We describe a prospective randomized-controlled single-centre trial in a tertiary referral centre. The primary outcome is the Comprehensive Complication Index (CCI) at 90 days after surgery. The CCI expresses morbidity on a continuous numeric scale from 0 (no complication) to 100 (death) by weighing all postoperative complications according to the Clavien-Dindo classification for their respective severity.

In the intervention group, patients will be instructed by physiotherapists to perform inspiratory muscle training containing of 30 breaths twice a day for at least 2 weeks before surgery using Power®Breathe KHP2. Depending on the surgical schedule, training can be extended up to 6 weeks. In the control group, no preoperative inspiratory muscle training will be performed. After the operation, both groups receive the same physiotherapeutic support.

**Discussion:**

Existing data about preoperative inspiratory muscle training on postoperative complications are ambiguous and study protocols are often lacking a clear design and a clearly defined endpoint. Most studies consist of multi-stage concepts, comprehensively supervised and long-term interventions, whose implementation in clinical practice is hardly possible. There is a clear need for randomized-controlled studies with a simple protocol that can be easily transferred into clinical practice. This study examines the effortless adjustment of the common respiratory physiotherapy from currently postoperative to preoperative. The external measurement by the device eliminates the diary listing of patients’ performances and allows the exercise adherence and thus the effect to be objectively recorded.

**Trial registration:**

ClinicalTrials.govNCT04558151. Registered on September 15, 2020.

## Administrative information

Note: the numbers in curly brackets in this protocol refer to SPIRIT checklist item numbers. The order of the items has been modified to group similar items (see http://www.equator-network.org/reporting-guidelines/spirit-2013-statement-defining-standard-protocol-items-for-clinical-trials/).

## Introduction

### Background and rationale {6a}

Postoperative pulmonary complications are frequent and have a significant impact on patient morbidity and mortality. These complications are particularly common after major abdominal procedures and can be considerable. The connection is likely that major abdominal surgery temporarily reduces respiratory function due to reduction of diaphragmatic strength caused by pain, anaesthesia and inhibitory reflexes as a consequence of splanchnic organ manipulation [1]. This reduction may be adequate to lead to complications or to not be able to ward off infections sufficiently. Pulmonary complications increase not only the length of hospital stay, medical consumption, thus suffering and costs [2–4], they are also the main reason for readmissions to critical care units after major surgery [5].

Inspiratory training is a cornerstone of postoperative physiotherapy and has been performed routinely for a long time [6]. The purpose of all inspiratory muscle training in any exercise regimen is to strengthen the muscles and increase breathing volume, thus leading to better physiological reserve. By inspiring against individual resistance, the muscles progressively strengthen by regular training, which may result in improved respiratory capacity [7]. In order to improve the reserves even before an operation—in the consideration of being more resistant with better reserves—physiotherapeutic regimes and studies are increasingly shifting from post- to preoperative [8, 9].

Most studies consist of multiple-component structured programs [10] including nutritional adaptations, high-intensity interval training, and supervised training sessions [11, 12]. The training span of different prehabilitation regimens is wide with a range from one to 6 weeks [13, 14]. However, implementation in clinical practice of these complex training schedules is hardly possible.

While systematic reviews have shown an advantage of these multi-step concepts regarding hospital length of stay, studies evaluating exclusively specific respiratory components are scarce [15, 16].

Recently, a systematic review has attempted to generate evidence about preoperative inspiratory muscle training [17] but the validity of the data remains controversial [18]. To date, there is no evidence from randomized-controlled trials to provide sufficient conclusions. There is a clear need for randomized-controlled studies with a simple protocol that can be easily transferred into clinical practice. Moreover, studies including different lengths of prehabilitation interventions are needed to investigate the impact of intervention duration [19].

Our study examines the effortless adjustment of the common respiratory physiotherapy from currently postoperative to preoperative. The external measurement by the device eliminates the diary listing of patients' performances and allows the exercise adherence and thus the effect to be objectively recorded.

### Objectives {7}

The aim of the study is to assess the impact of preoperative inspiratory muscle training on postoperative overall morbidity. The question is whether inspiratory muscle training prior to elective surgery reduces the number of postoperative complications and their severity grade.

The primary objective is to show in patients with elective major abdominal surgery that inspiratory muscle training before surgery compared to no pre-operative training reduces the number and severity of postoperative complications, as assessed by the Comprehensive Complication Index.

The secondary objective is to investigate in patients with elective major abdominal surgery whether inspiratory muscle training before surgery compared to no pre-operative training affects: postoperative outcome and physiotherapeutic changes.

### Trial design {8}

This is a prospective randomized-controlled single-centre open-label trial with a 1:1 allocation. The framework of the study is designed to test the superiority of preoperative inspiratory muscle training on postoperative complications in abdominal surgery.

## Methods: participants, interventions and outcomes

### Study setting {9}

The study takes place in a university hospital in Switzerland (Ref: University Hospital Zurich USZ)

### Eligibility criteria {10}

#### Inclusion criteria

Informed consent as documented by signature.Planned abdominal surgery with planned duration > 2 h.Planned surgery at least 2 weeks after inclusion at the outpatient clinic.Adult patient over 18 years.

#### Exclusion criteria

Inability to follow the procedures of the study, e.g. due to language problems, psychological disorders, dementia, of the participant.Known or suspected non-compliance to the study, drug or alcohol abuse.Previous enrolment into the current study.Participation in another study with inspiratory muscle training within 30 days preceding or during this study.Participation in another study with investigational drugs within 30 days preceding or during this study.Planned two-stage hepatectomies (e.g. ALPPS).

### Who will take informed consent? {26a}

The investigators will explain to each participant the nature of the study, its purpose, the procedures involved, the expected duration, the potential risks and benefits and any discomfort it may entail. Each participant will be informed that the participation in the study is voluntary and that he/she may withdraw from the study at any time and that withdrawal of consent will not affect his/her subsequent medical assistance and treatment. Enough time needs to be given to the participant to decide whether to participate or not.

The formal consent of a participant, using the approved consent form, will be obtained before the participant is submitted to any study procedure by one of the investigators.

### Additional consent provisions for collection and use of participant data and biological specimens {26b}

On the consent form, participants will be asked if they agree to use of their data should they choose to withdraw from the trial. Participants will also be asked for permission for the research team to share relevant data with people from the Universities taking part in the research or from regulatory authorities, where relevant. This trial does not involve collecting biological specimens for storage.

## Interventions

### Explanation for the choice of comparators {6b}

It is current standard not to perform any physiotherapeutic intervention or respiratory training before surgery.

The training of inspiratory muscles is the cornerstone of postoperative physiotherapy. The change of this simple but effective treatment to the preoperative setting was driven by the known effect and the simplicity of the intervention. In the postoperative setting, the use of pressure threshold inspiratory muscle training devices is meanwhile well-established in clinical practice.

The intervention regimen follows physiotherapeutic standards and instructions are given by a specialized physiotherapist. No additional training of physiotherapists is required due to the fact that the preoperative training is identical with the postoperative one. Training of inspiratory muscles can be performed in an outpatient setting. The training session is performed unsupervised, during the period of preoperative training, a reassessment of the physiotherapist will be undertaken to ensure adherence to training. Two weeks of preoperative training is the assumed minimum to see an effect. At the same time, this interval is very usual in a clinical routine; a longer training would maybe show a more pronounced effect but could probably never be implemented. The possibility of its implementation in daily routine is main reason why we decided to examine a simple procedure in a manageable time frame.

To perform 30 breath twice a day is the usual practice of POWER®breathe.

### Intervention description {11a}

Once patients give their informed consent to the study and are assigned to the intervention group, physiotherapists will measure the maximal inspiration pressure (MIP) with the POWER®breathe device of each single patient. Patients will then be instructed to perform inspiratory muscle training at the level of 60% of their MIP. Patients are instructed to perform the training containing 30 breaths twice a day for 14–18 days before surgery. After 7 days of training, a physiotherapeutic control will be performed to check compliance and training performance and to answer open questions. The devices are able to register the performance of each single training session and training results are monitored.

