## Participant timeline {13}

The participant timeline is shown in Table 1.

**Table 1 Tab1:** Participant timeline

***Visit***	***1***	***2***	***3***	***4***		***6***	***7***	***8***
*Time (day)*		***0***	***7 +/-2d*** ^***a***^	***14 +/-4d***	*0*	***5+/-2d pod***	***x pod***	***90+/-14 pod***
*Patient schedule*	***Screening visit***	***Baseline visit***	***Compliance visit***^a^	***Admission to hospital***	***Surgery***	***Day 5 after surgery***	***End of hospitalisation***	***End of study visit***
*Hospital status*	*Outpatient*				*Inpatient*			*Outpatient clinic*
*Patient information and informed consent*	*x*							
*Demographics*	*x*							
*Medical history*	*x*			*x*				
*Medication*^b^	*x*			*x*			*x*	
*In-/exclusion criteria*	*x*	*x*						
*Administer medical device and training instruction*		*x*						
*Inspiratory muscle training (IMT)*		x	*x*	*x*				
*Power®Breathe device*		*KHP2*^*c*^*,KH2*	*KHP2*	*KHP2*^d^		*KH2*		
*Compliance check and training performance*			*x*					
*VAS/NRS/ Vital signs*				*x*		*x*	*x*	
*BMI*	*x*			*x*				
*Maximum inspiratory pressure*		*x*		*x*		*x*		
*Load (cmH20), Power (Watt), Breathing Energy (Joule), Volume (l)[measured by Power®Breathe device*]		*x*	*x*	*x*		*x*		
*Sit-to-stand test*		*x*		*x*		*x*		
*(Serious) Adverse events*		*x*	*x*	*x*		*x*	*x*	*x*
*Complications*							*x*	*x*

^a^When IMT (inspiratory muscle training) > 15 days, patients are offered an additional appointment with physio on demand, scheduled training can be extended up to 6 weeks

^b^Antibiotics, immunosuppressants, anticoagulants, insulin, oral antidiabetics

^c^Hand out Power®Breathe KHP2 device by a physiotherapist to patient

^d^Return of Power®Breathe KHP2 device to the physiotherapist on the ward

*pod* postoperative day, *VAS* visual analogue scale, *NRS* numerical rating scale, *BMI* body mass index

Control group starts at Visit4: hospital admission. The postoperative procedure is the same for both groups

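### Table 1 lets admission and device return fall on days 10 to 13, short of the two-week training minimum, and the 36-session device store cannot hold a 6-week course

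*Protocol article*

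**What the plan says.** **Duration of training.** The abstract (Methods) asks for "30 breaths twice a day for at least 2 weeks before surgery" and adds: "Depending on the surgical schedule, training can be extended up to 6 weeks". The rationale under Explanation for the choice of comparators {6b} states: "Two weeks of preoperative training is the assumed minimum to see an effect". Intervention description {11a} gives the working instruction: "Patients are instructed to perform the training containing 30 breaths twice a day for 14–18 days before surgery".

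**Visit schedule.** In Table 1 (Participant timeline {13}) the device is handed out and training begins at the baseline visit, day 0. A compliance visit (Visit 3) follows on day 7 plus or minus 2. Visit 4, hospital admission, is on day 14 plus or minus 4, and its footnote d reads: "Return of Power®Breathe KHP2 device to the physiotherapist on the ward". Footnote a, attached to Visit 3, says that when training runs past 15 days "patients are offered an additional appointment with physio on demand, scheduled training can be extended up to 6 weeks". The note below the table adds: "Control group starts at Visit4: hospital admission".

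**Eligibility.** The matching inclusion criterion is: "Planned surgery at least 2 weeks after inclusion at the outpatient clinic". Recruitment {15} has the physiotherapist explain the training at a separate meeting.

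**Adherence record.** Strategies to improve adherence {11c} says that the device registers every session and keeps all results, that patients are telephoned regularly, and that they need keep no log of their own. The retention section {18b} gives the device's capacity as 36 sessions. Statistical methods {20a} makes membership of the per-protocol set depend on a minimum level of training compliance.

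**The concern.** The schedule and the dosing text disagree at the lower end. A patient admitted on day 10 has kept every visit on time, yet has trained for less than the period that the protocol itself treats as the least that could work. If surgical slots come early, the trial can deliver a weaker intervention than the one it sets out to test while its visit schedule is fully met.

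The record has a different problem. The Discussion names device-recorded adherence as a strength of the study, and the per-protocol set relies on training compliance. The store is sized for the standard course. In a course extended towards 6 weeks it fills up, no read-out after Visit 3 is scheduled, and there is no diary to fall back on. The patients who train longest could then have the least complete records.

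**Working it through.** **Inputs from the protocol**
- Two sessions a day for 14 to 18 days ({11a}); minimum 14 days (abstract; {6b}).
- Visit 3 on day 7 ± 2 and Visit 4 on day 14 ± 4, counted from baseline (Table 1).
- Extension to 6 weeks (abstract; Table 1, footnote a).
- Store of 36 sessions ({18b}).

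**Assumed, because not stated**
- Whether day 0 and the admission day count as training days (both conventions are shown).
- The intervals from inclusion to baseline and from admission to surgery.
- That the device is read out and cleared at Visit 3.

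**Step 1: the standard course.** 2 × 14 = 28 sessions and 2 × 18 = 36 sessions. The store lasts 36 / 2 = 18 days, so it fits the upper end of the standard regimen exactly.

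**Step 2: the Visit 4 window.** 14 − 4 = day 10; 14 + 4 = day 18. The upper end agrees with {11a}; the lower end does not.

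**Step 3: does eligibility protect the minimum?** Take surgery planned exactly 14 days after inclusion. Let g be the days from inclusion to baseline plus the days from admission to surgery. Baseline to admission is then 14 − g days. With g = 1, 2, 3 or 4, admission falls on day 13, 12, 11 or 10. If baseline is held on the day of inclusion, any admission before the day of surgery still makes g at least 1.

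**Step 4: sessions delivered, against 28**

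| Admission day | One end day counted: 2 × day | Short by | Both end days counted: 2 × (day + 1) | Short by |
|---|---|---|---|---|
| 10 | 20 | 8/28 = 29% | 22 | 6/28 = 21% |
| 11 | 22 | 6/28 = 21% | 24 | 4/28 = 14% |
| 12 | 24 | 4/28 = 14% | 26 | 2/28 = 7% |
| 13 | 26 | 2/28 = 7% | 28 | 0% |

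**Step 5: the store in a 6-week course.** 42 days × 2 = 84 sessions. With no read-out before return, 84 − 36 = 48 sessions exceed the store. With a read-out and clearing at Visit 3 on day v, 2 × (42 − v) sessions remain, 2 × (42 − v) − 36 of them are not held, and the store is full on day v + 18:

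| Visit 3 on day | Done | Remaining | Not held | Share of 84 | Store full on day |
|---|---|---|---|---|---|
| 5 | 10 | 74 | 38 | 45% | 23 |
| 7 | 14 | 70 | 34 | 40% | 25 |
| 9 | 18 | 66 | 30 | 36% | 27 |

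**Step 6: when a further read-out is needed.** To cover 42 days with one more read-out on day d, d must be at most v + 18 and at least 42 − 18 = 24. With Visit 3 on day 7, d is 24 or 25. With Visit 3 on day 9, d is 24 to 27. With Visit 3 on day 5 the limit is day 23, so a full 42-day course would need two further read-outs.

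**The case against.** The strongest reply is that a visit tolerance is not a dosing rule. That is largely right, and it limits the point. A reader might infer that under-dosing would go unnoticed. The documents do not support this: {11a} still sets 14 to 18 days, and a course of 10 to 13 days produces 20 to 28 sessions, which fit in the store, so the log would show a short course. What stands is that the schedule accepts a date the dosing text does not.

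A reader might also infer that the day-18 upper limit contradicts the 6-week extension. The two can be read as default and exception, and footnote a sits in the same table. Only a cross-reference from Visit 4 is missing, which is editorial.

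The shortfall needs surgery at or near the two-week boundary plus some days lost at either end. Neither interval is given, and a separate meeting need not be on a separate day. So the frequency is unknown, but the eligibility rule still measures a different interval from the training period.

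On storage, a condensed article may leave read-out procedures to the full protocol, and whether a full device overwrites or stops is not stated. It would therefore be wrong to say that data will be lost. But the article does state that all results are kept, and its own capacity figure does not support that for an extended course without a read-out in between. The regular telephone calls support adherence; nothing says that they retrieve session data.

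**Conclusion.** Wrong as written, of minor severity. Two statements need correction: the lower end of the Visit 4 window, which admits up to four days less than the stated minimum, and the claim of complete storage, which holds for the standard course but not for one extended to 6 weeks unless the device is emptied on the way.

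The sizes are conditional. The shortfall of 0% to 29% depends on the admission day and on which end days count. The 30 to 38 sessions not held depend on a full 42-day course, clearing at Visit 3 and no read-out after it. How many patients fall in either group is not stated.

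The effect is on delivered dose and on the adherence record behind the per-protocol set. A reader might go further and infer a flaw in the primary analysis or the power. That does not follow: the full analysis set keeps every randomized patient as allocated, and none of the sample-size inputs (difference 6, SD 10, alpha 5%, power 90%, drop-out 10%) is a training duration.

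**What to change.** 1. **Visit 4 window.** Set the lower limit at day 14 from baseline, with a target of 14 to 18 and up to day 42 when training is extended. Attach footnote a to Visit 4, refer to the extension in {11a}, and say whether day 0 and the admission day count.
2. **Secure the days.** Before randomization, confirm for every candidate that planned admission is at least 14 days after the intended baseline visit, or hold baseline at inclusion. The date check must come before allocation and apply to both arms alike: controls have no visit before admission, so a later check would act on one arm only.
3. **Early admissions.** Record them as deviations and keep the patients in the full analysis set.
4. **Extended training.** Turn the on-demand appointment into a scheduled read-out and clearing at least every 18 days. With Visit 3 on day 7, one on day 24 or 25 covers all 42 days.

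**Cost.** A clarification submitted to the ethics committee and applied to later patients, since recruitment has begun. Scheduling becomes slightly tighter, and each patient with a long extension usually needs one more read-out. Under the date check, some candidates with surgery at the two-week boundary would not be randomized. Moving the window alone adds no training days; it is the date check or the early baseline visit that helps to secure them.

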### Criteria for discontinuing or modifying allocated interventions {11b}

Patients are withdrawn from the study when they withdraw their informed consent. There will be no special criteria for discontinuing or modifying allocated interventions.

### Strategies to improve adherence to interventions {11c}

The POWER®breathe KHP2 devices are able to register the performance of each single training session so that all training results are stored. Furthermore, we are calling the patient on a regular basis, to improve adherence or to detect potential problems. Patients will not have to keep up-to-date records of their training.

### Relevant concomitant care permitted or prohibited during the trial {11d}

There are no specific interventions that would be prohibited during the trial except participation in another study that could interfere with the inspiratory muscle training.

### Provisions for post-trial care {30}

Insurance is covered by “Versicherung für klinische Versuche und nichtklinische Versuche” by Zurich Versicherungs-Gesellschaft AG.

Any damage developed in relation to study participation is covered by this insurance. So as not to forfeit their insurance cover, the participants themselves must strictly follow the instructions of the study personnel. Participants must not be involved in any other medical treatment without permission of the principal investigator (emergency excluded). Medical emergency treatment must be reported immediately to the investigator. The investigator must also be informed instantly, in the event of health problems or other damages during or after the course of study treatment.

The investigator will allow delegates of the insurance company to have access to the source data/documents as necessary to clarify a case of damage related to study participation. All involved parties will keep the patient data strictly confidential.

A copy of the insurance certificate will be placed in the Investigator’s Site File.

